**Figure 1 F1:**
[figure not shown]
**Overview of the voting process in the final round of the modified Delphi task. ***Note.* In the third and final round of the modified-Delphi task, expert panelists will vote on all strategies where concerns were raised regarding the core definition in the first two online survey rounds. For each strategy, the original and proposed alternate definitions will be presented for an approval poll in which participants can vote to approve all definition alternatives that they find acceptable. In the first round of voting, if one definition receives a supermajority of votes (≥60%) and receives more votes than all others, that definition will be declared the winner and the poll will move to the next term. If there is no consensus, a five-minute discussion period is opened. When the discussion concludes, a run-off poll is conducted to determine the most acceptable definition alternative.

In the first round of voting, if one definition receives a supermajority of votes (≥60%) and receives more votes than all others, that definition will be declared the winner and the poll will move to the next term. Approval poll results will be presented to the panelists in real time. If there is no clear supermajority winner, then panelists will have the opportunity to discuss the definitions. Panelists will indicate whether they would like to talk using a virtual hand raise button in the webinar platform. When addressed by the webinar moderator, the participant will have up to one minute to make comments. Discussion will be limited to five minutes per strategy. This discussion duration was chosen for two reasons. First, Rounds 1 and 2 of the modified Delphi process provide participants with the opportunity for unlimited comments, and this feedback influences what is provided in Round 3. Second, the Round 3 webinar will be targeted to last about 60 minutes to improve panelist participation rate and minimize participant burden.

The second round of voting involves a ‘runoff vote’ in which participants will select only their top choice. If there are only two choice alternatives, then the definition receiving the most votes will be declared the winner. If there are three or more choices, two rounds of runoff voting will occur. The first runoff round will determine the top two definitions for the strategy, and the second runoff round will determine the winner. If a tie occurs between the original and alternative definition in the runoff round, the definition already published in the literature will be retained.

For strategies introduced by the expert panel in modified Delphi Rounds 1 and 2, the approval poll will include a ‘reject’ option for the proposed strategy. A supermajority (≥60%) of participants will be needed to reject a proposed strategy. Aside from the reject option, the same approval and runoff voting procedures will be followed as described above.

### Stage 2: Concept mapping

A practical challenge faced when asking experts to consider a large number of concepts while making recommendations is how to structure the presentation of the concepts to minimize the cognitive burden of an already complex task. One strategy to ease cognitive burden when making recommendations is to place strategies into categories to facilitate the consideration of strategies that are similar. The purpose of Stage 2 is to develop categorical clusters of strategies based on how the expert panelists view the relationships among the strategies.

To achieve this purpose, a concept mapping exercise will be used. Concept mapping is considered a substantially stronger methodological approach for characterizing how complex concepts are organized than less structured group consensus methods [66]. Concept mapping in this project will utilize the Concept Systems Global MAX© web platform for participation and data analysis. Participants will first be asked to sort virtual cards of strategies into piles that make sense to them and provide names for the piles created using the web-based platform [67]. Then, panelists will rate each discrete implementation strategy in terms of its importance and feasibility [68-70]. The instructions for the importance rating will be as follows:

Please select a number from 1 to 5 for each discrete implementation strategy to provide a rating in terms of how important you think it is. Keep in mind that we are looking for relative importance; use all the values in the rating scale to make distinctions. Use the following scale: 1 = Relatively unimportant; 2 = Somewhat important; 3 = Moderately important; 4 = Very important; 5 = Extremely important.

Third, participants will provide a feasibility rating for each strategy. The instructions for the feasibility rating were as follows:

Please select a number from 1 to 5 for each discrete implementation strategy to provide a rating in terms of how feasible you think it is. Keep in mind that we are looking for relative feasibility; use all the values in the rating scale to make distinctions. Use the following scale: 1 = Not at all feasible; 2 = Somewhat feasible; 3 = Moderately feasible; 4 = Very feasible; 5 = Extremely feasible.

Prior to participating, panelists will be provided with an instruction sheet (Additional file 4) and the final compilation of the discrete implementation strategies and their core definitions from Stage 1.

The study’s planned minimum enrollment of 20 is above the recommended sample size for concept mapping (≥15) [71]. In this stage, multidimensional scaling and hierarchical cluster analysis will be used to characterize how implementation terms were clustered by panelists, providing the opportunity to quantitatively characterize the categories of terms developed by the panel in terms of how they were rated on key dimensions.

Final data analyses will include visual summaries of data including weighted and unweighted cluster maps, ladder graphs, and go-zone graphs, all specific tools from the web platform used for this analysis [66,68]. Cluster maps provide a visual representation of the relatedness of concepts, and weighted cluster maps are used to depict how concepts within a cluster were rated on key dimensions (*e.g.*, importance). Ladder graphs provide a visual representation of the relationship between dimensions of a concept (*e.g.*, importance and feasibility, importance and changeability). Go-zone graphs are useful for illustrating the concepts that are most actionable (*e.g.*, high importance and high feasibility) and which concepts are less actionable (low importance and low feasibility). Bridge values (*i.e.*, quantitative characterizations of how closely individual concepts within a cluster are related) will also be reported. These summaries will be provided to the Expert Panel for consideration while participating in Stage 3 activities.

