### Study aims

This mixed methods study will address the aforementioned gaps related to conceptual clarity and selection of implementation strategies through the following aims:

### Aim 1

To establish consensus on a common nomenclature for implementation strategy terms, definitions and categories that can be used to guide implementation research and practice in mental health service settings.

### Aim 2

To develop a set of recommendations that specifies implementation strategies likely to be effective in integrating EBBPs into VA mental health service settings.

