## Methods/Design

### Overview

The ERIC process involves a four-stage sequential mixed methods design (qualitative → QUANTITATIVE) [57]. Stages 1 and 2 are used to establish expert consensus on a common nomenclature for implementation science (Aim 1). Stages 3 and 4 build upon the earlier stages and are used to develop expert recommendations regarding how to best match discrete implementation strategies to high priority implementation scenarios in mental health (Aim 2). Table 1 provides an overview of the study’s aims and stages. Qualitative methods are used to develop expert recommendations, and quantitative methods are used to guide the recommendations by obtaining ratings of implementation strategies (alone and as applied to example implementation scenarios), providing structured feedback to the expert panel, and characterizing the consensus process.

**Table 1 T1:** Overview of the four stages of the ERIC process

	**Stage**	**Input**	**Task**	**Output**
**Aim 1**	Stage 1	Refined compilation of discrete implementation strategies	Modified Delphi, 2 feedback rounds and consensus meeting	•Expert consensus on key concepts (definitions & ratings)
	Modified Delphi			
	Stage 2	Post-consensus compilation of discrete implementation strategies	Sort the strategies in to subcategories; rate each strategy in terms of importance and feasibility	•Weighted and unweighted cluster maps
	Concept Mapping			•Ladder maps
				•Go-zone graphs
				•Importance and feasibility ratings for each strategy
**Aim 2**	Stage 3	•Discrete implementation strategies	Essential ratings are obtained for each strategy for three temporal frames given each scenario	For each practice change:
	Menu-Based Choice	•Practice change narrative		•Relative Essentialness Estimates for each strategy given each scenario
		•Narratives of contextual variations of practice change scenarios		•A rank list of the most common strategy recommendation combinations
				•A summary of strategies that may serve as compliments and substitutes for each other
	Stage 4	•Menu-Based Choice data summaries for each scenario	Facilitated discussion; live polling of consensus reached during discussion	For each practice change:
	Facilitated Consensus Meeting	•Importance and feasibility ratings from the concept mapping task		•Expert consensus regarding which discrete implementation strategies are of high importance
				•Context specific recommendations

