### Stage 4: Web-based facilitated expert recommendation process

A live web-based facilitated expert recommendation process will be employed in Stage 4. Separate webinars will be hosted for each of the three practice changes. Prior to the webinar, respondents will be provided with the following materials for each scenario: a description of the scenario for continued reference; a personal summary of the essential ratings he or she provided for each implementation strategy at each temporal phase of implementation; and group data describing numerical and graphical descriptive analyses of the most commonly selected combinations of essential strategies, itemization of strategies qualifying as substitutes or compliments, the REE of each strategy, and Stage 2 importance and feasibility ratings of each strategy. During the interactive webinar, study investigators will facilitate a general discussion of the summary material provided to panelists in preparation for developing recommendations for which implementation strategies are essential at each of the three temporal phases in the particular scenarios. This will be followed by scenario-specific facilitated discussions of the top five essential strategy combinations obtained in Stage 3. Live polling will be used to document the degree of consensus for the final recommendations for each scenario. Polling will commence one scenario at a time, addressing each temporal phase of implementation separately, one conceptual cluster of strategies at a time, presenting the top five essential strategy combinations plus any additional combinations identified as highly preferable during the facilitated discussion. Poll results will be used to characterize the expert panel’s rate of consensus for the final set of recommendations regarding which discrete strategies are essential for each phase of implementation for a particular implementation scenario.

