## Discussion

This multi-stage mixed methods study will produce consensus on a common nomenclature for implementation strategy terms, definitions, and their categories (Aim 1) and yield contextually sensitive expert recommendations specifying which implementation strategies are likely to be effective in supporting specific practice changes (Aim 2) as listed in Table 1. This study will use innovative technology to engage multiple stakeholder experts (*i.e.*, implementation scientists and clinical managers). First, the three-round modified Delphi procedure will involve input through two rounds of online surveys followed by one virtual webinar meeting, targeting only the strategies where consensus concerns were noted in the first two rounds. The virtual nature of this and subsequent ERIC activities decreases the logistical hurdles involved in obtaining involvement from high-level stakeholders.

Second, a web-based concept mapping platform will be used to capture how expert panelists rate the importance and feasibility of the implementation strategies, as well as how the strategies are conceptually organized. This latter output is particularly important because the number of discrete implementation strategies that can be considered for any particular practice change initiative is vast, and conceptual organization of the strategies is essential for supporting the expert recommendation process.

Third, while the concept mapping exercise includes an assessment of each discrete implementation strategy’s importance and feasibility, these represent global ratings rather than context-specific recommendations. To obtain preliminary, context-specific recommendations for three phases of implementation (pre-implementation, active implementation, and sustainment), a series of MBC tasks will elicit expert recommendations for collections of recommended strategies to address the needs for each of three real-world implementation scenarios. Aggregate data from this exercise will produce quantitative characterizations of high and low levels of consensus for individual strategies at each phase of implementation for each scenario.

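### Expert consensus on strategy categories is promised, but Stage 2 as described aggregates individual sorts and applies no agreement criterion, so the consensus claim for categories is unsupported and could not fail

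*Protocol article*

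**What the plan says.** Study aims gives Aim 1 as: "To establish consensus on a common nomenclature for implementation strategy terms, definitions and categories". The abstract's Background paragraph makes the same promise. The Discussion says that the study "will produce consensus on a common nomenclature for implementation strategy terms, definitions, and their categories (Aim 1") and repeats the idea later, where it describes ERIC as two packages. The Overview credits both stages: "Stages 1 and 2 are used to establish expert consensus on a common nomenclature for implementation science (Aim 1").

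For definitions, Stage 1 sets out how agreement is reached: an approval poll with a bar of at least 60%, a timed discussion, runoffs and a tie rule.

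For categories, Stage 2 gives this purpose: "The purpose of Stage 2 is to develop categorical clusters of strategies based on how the expert panelists view the relationships among the strategies". Panelists "sort virtual cards of strategies into piles that make sense to them and provide names for the piles created", and then rate importance and feasibility. In the analysis, "multidimensional scaling and hierarchical cluster analysis will be used to characterize how implementation terms were clustered by panelists". Maps, graphs and bridge values follow, and the summaries go to the panel to consider during Stage 3.

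Table 1 in the Overview lists this as the Stage 1 output: "Expert consensus on key concepts (definitions & ratings"). The Stage 2 outputs are maps, graphs and ratings. The word consensus returns only at Stage 4, for which strategies are of high importance.

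**The concern.** Agreement on categories is part of what Aim 1 sets out to achieve, yet no described step measures it against a standard. Nobody is asked whether the cluster membership or labels are acceptable, and no level of agreement is named. Hierarchical clustering divides any set of items into clusters, whether the panelists sorted alike or not. If obtaining clusters is taken as obtaining consensus, that part of Aim 1 is met whatever the data show.

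What is at stake is what the study may conclude. A published statement that experts agreed on the categories would carry more weight than the method gives it, and readers could not tell a category that most panelists recognised from one that the algorithm assembled out of divergent sorts.

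**Working it through.** **1. Claim against method.** The article states no figure for this point, so there is none to reproduce. Its statements side by side:

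| Place in the article | What is said about categories |
|---|---|
| Abstract, Background; Study aims; Discussion (twice) | Consensus covers categories |
| Overview, text | Stages 1 and 2 together establish the consensus of Aim 1 |
| Overview, Table 1 | Consensus listed for Stages 1 and 4, not for Stage 2 |
| Abstract, Methods/Design | Stage 1 gives consensus on terms and definitions; Stage 2 yields categories |
| Background, section on lack of conceptual clarity | Consensus on terms and definitions; categories are developed |
| Stage 2 | Individual sorting, scaling, clustering, bridge values; no vote, review or threshold |

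The first two rows claim more than the last four describe.

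**2. Does a cluster solution show agreement?** Inputs from the article: 20 panelists (minimum enrollment) and 68 strategies (the starting compilation, before Stage 1 changes). Assumptions, because the article does not give them: 10 piles per panelist, classical two-dimensional scaling, Ward linkage, and a cut at k = 5, 9 or 12 clusters. A fraction s of placements follows one shared structure and the rest are random. Each setting was run 200 times.

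For strategies i and j, co-sorting = (number of panelists who put i and j in the same pile) / 20. The table gives its mean over pairs in the same cluster. Silhouette = (b − a) / max(a, b), where a is the mean map distance to the strategy's own cluster and b that to the nearest other cluster. It measures how separate the clusters look on the map. Chance co-sorting is 1/10 = 10%.

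| Shared fraction s | k | Clusters returned | Within-cluster co-sorting | Mean silhouette |
|---|---|---|---|---|
| 0 | 5 | 5 | 12.5% | 0.356 |
| 0 | 9 | 9 | 12.9% | 0.378 |
| 0 | 12 | 12 | 12.9% | 0.390 |
| 0.3 | 5 | 5 | 13.3% | 0.372 |
| 0.3 | 9 | 9 | 13.9% | 0.384 |
| 0.3 | 12 | 12 | 14.1% | 0.400 |
| 0.5 | 5 | 5 | 17.4% | 0.471 |
| 0.5 | 9 | 9 | 20.8% | 0.433 |
| 0.5 | 12 | 12 | 20.9% | 0.423 |
| 0.8 | 5 | 5 | 28.9% | 0.609 |
| 0.8 | 9 | 9 | 42.4% | 0.553 |
| 0.8 | 12 | 12 | 44.2% | 0.500 |

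The requested number of clusters came back in every run, including those with no shared view. The look of the map is a weak guide: at k = 12, the silhouette moves only from 0.390 with no shared view to 0.423 when half the placements are shared. Co-sorting over the same step goes from 12.9% to 20.9%.

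**3. Is there a natural threshold?** At s = 0.8, two strategies from the same shared pile are expected to be co-sorted by 0.8² + (1 − 0.8²) × 0.1 = 0.64 + 0.036 = 67.6% of panelists. Two from different shared piles are expected at 0.36 × 0.1 = 3.6%. The observed means of 29% to 44% lie between these because clusters on the map mix strategies from different piles. So 60% (12 of 20 panelists), which serves for choosing between definitions, does not carry over to co-sorting.

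**The case against.** **The article already makes the distinction.** This is largely right. The abstract's methods paragraph and the Background keep consensus for terms and definitions and speak of developing categories, and Stage 2 justifies concept mapping as a stronger way to characterize how concepts are organized than less structured group consensus methods. The choice of method is deliberate and is not faulted here. But characterizing a panel's views differs from showing that the panel agrees, and the formal aim and the Discussion claim the latter.

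**Bridge values cover agreement.** In part. They will be reported and readers can use them. The article defines them as relatedness of concepts within a cluster and ties no criterion or decision to them.

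**A condensed article leaves such details to the full protocol.** This holds for linkage, stress and the rule for the number of clusters, none of which is counted here. The point rests on what the article states: its aim and its described method do not match.

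**The simulation is extreme.** Twenty experts sorting at random is not a forecast. It shows only that obtaining clusters is not evidence of agreement.

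Three stronger readings are tempting, and the article does not support them:

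- *The categories are merely an algorithm's product.* They aggregate the panel's own sorts, with piles that the panelists named.
- *No percentage agreement could be reported.* It can be computed directly from the sort data. It is simply not planned or required as described.
- *Contested clusters distort the Aim 2 recommendations.* Stage 4 does poll "addressing each temporal phase of implementation separately, one conceptual cluster of strategies at a time", in up to 3 practice changes × 3 scenarios × 3 phases = 27 cells per cluster. That counts where clusters appear and is not an effect. In Stage 3 every strategy is visible and rated individually, the Relative Essentialness Estimate has no cluster term, and Stage 4 allows combinations raised in discussion to be added.

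**Conclusion.** The point holds as a mismatch between claim and method. Consensus on categories is promised in the abstract, Aim 1 and the Discussion, and by implication in the Overview. Stage 2 as described could neither show it nor fail to show it. Its size is the reach of one conclusion, the category part of Aim 1. Consensus on terms and definitions, the panel size and the Aim 2 procedure are untouched, and harm to the recommendations is not shown.

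The conclusion rests on the described Stage 2 being complete as to whether the panel ratifies the clusters. The fact that clustering returns the number of clusters asked for does not depend on the simulation's assumptions. The co-sorting and silhouette values do (pile count, linkage, scaling variant, k) and are illustrative only.

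**What to change.** 1. Reword the abstract's Background, Aim 1, the Overview sentence and both Discussion statements to match the abstract's methods paragraph and the Background: consensus on terms and definitions, and categories derived from panel sorting. This costs only editing.
2. Report for each cluster the mean within-cluster co-sorting percentage beside the bridge values, so that readers can see how far the panel agreed. The sorts are collected anyway, so the cost is a short computation.
3. If the consensus claim on categories is to be kept, add a brief asynchronous panel review of the draft clusters, their members and labels before Stage 3, with an agreement level set in advance and the result reported per cluster. The level need not be 60%. The cost is some panelist time and a short delay before Stage 3.

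Items 1 and 2 together are sufficient. Item 3 is needed only if the stronger claim is wanted, and it would then replace the rewording in item 1.

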### Stage 3: menu-based choice tasks

Stage 3 involves Menu-Based Choice (MBC) tasks. MBC tasks are useful for providing a context rich structure for making decisions that involve multiple elements. This method emulates naturalistic choice conditions and allows respondents to ‘build their own’ products. To our knowledge, this is the first time an MBC task has been used in an expert recommendation process. We decided to utilize this method because of its transparency, structural characteristics that support decision-making involving a large number of choices, and the ability to quantitatively represent the recommendations. The latter component, described below, will support a more structured dialogue for the final meeting to develop recommendations in Stage 4.

In the MBC tasks, panelists will be presented with the discrete strategies refined in Stages 1 and 2, and they will build multi-strategy implementation approaches for each clinical practice change being implemented. Within each practice change, three scenarios will be presented that vary in terms of implementation relevant features of the organizational context (*e.g.*, organizational culture, leadership, evaluation infrastructure) [44]. Project staff will construct the practice setting narratives using the following multi-stage process. First, a VA Mental Health QUERI advisory committee comprised of operations and clinical managers will be asked to identify high priority and emerging areas of practice change for VA mental health services (*e.g.*, metabolic monitoring for patients taking antipsychotics, measurement-based care, psychotherapy practices). Second, project staff will construct narrative descriptions of specific practice changes (*e.g.*, improving safety for patients taking antipsychotic medications, depression outcome monitoring in primary care mental health, prolonged exposure therapy for treating post-traumatic stress disorder). Third, project staff will construct narrative descriptions of implementation scenarios with varying organizational contexts. Fourth, practice setting narratives will be sent to clinical managers who will be asked to: rate how similar each setting narrative is to their own clinical setting; rate how similar each setting narrative is to other known clinical settings at the VA; and identify descriptors that would improve the narrative’s match with their own or other known clinical settings at the VA. This feedback will be used to refine the content of the MBC tasks before distribution to the expert panel.

In the MBC tasks, panelists will indicate how essential each discrete implementation strategy is to successfully implement the practice changes described in each narrative, taking care not to burden the care system with unnecessary implementation tasks. Essential ratings (*i.e.*, absolutely essential, most likely essential, most likely inessential, absolutely inessential) will be dichotomized as essential and inessential for primary analyses used for panelist feedback. Panelists will provide essential ratings separately for three temporal frames (*i.e.*, pre-implementation, implementation, and sustainment) for each scenario. Strategies will be organized into clusters consistent with the categories identified in Stage 2 to help decrease the cognitive burden of this task [72]. This information will be placed in structured spreadsheets that support participants in considering multiple implementation strategies simultaneously. This structure is designed to improve participants’ ability to consider each strategy recommendation in relation to similar strategies while being able to view whether their recommendations are consistent or change based on timing and contextual features of each scenario (see Figure 2).

